### Study design and settings

We designed this study as a randomized, double-blind, single-simulated placebo-controlled clinical trial. The study will be conducted in the Department of Cardiology, Longhua Hospital, Shanghai University of Traditional Chinese Medicine, to achieve the goal of 76 participants with atrial fibrillation (qi deficiency and phlegm opacities) in total. The participants who fulfill both the inclusion and exclusion criteria will be recruited into the study. After participants signed the consent form, they will be randomly assigned to the treatment or control group. Participants in the treatment group will receive HTDJ, whereas those in the control group will receive placebo granules. The participants will continue to receive systemic therapy, as judged by their treating physician. All changes in symptoms, prescriptions, relevant scores, and macroscopic characteristics (based on photographic evidence), along with any adverse events (AEs), will be recorded. The experimental design is shown in Fig. 1.

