### Eligibility criteria

Eligible patients will be those who fulfill all of the following inclusion criteria and who do not have any of the listed exclusion criteria. The planned enrollment period is 12 weeks.

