### Exclusion criteria

The exclusion criteria are as follows: (1) patients with primary diseases such as severe lung, liver, renal insufficiency, and hematopoietic system or severe cardiac dysfunction (NYHA IV grade); (2) atrial fibrillation caused by obvious incentives such as fatigue, mental stress, mood swings, drug poisoning, and electrolyte disturbance; (3) mental illness and poor control of the condition; (4) patients whose heart rate is less than 50 beats per minute (such as sick sinus syndrome, atrioventricular, or intraventricular block, who intend to install a pacemaker); (5) pregnant or lactating women; (6) cachexia in the terminal stage of malignant tumor; and (7) for various reasons, the efficacy cannot be determined or the data is incomplete.

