### Randomization

This study uses a center-based stratification and block randomization method. The randomization sequence will be generated by study investigators who are statisticians. Patients will be allocated in a 1:1 ratio, aiming to balance baseline characteristics between the groups. Participants will be assigned a PID number, which will be used for subject identification throughout the study. Information regarding the random-number block will be delivered to the participating centers along with the intervention drugs.

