### Outcomes

#### Primary outcome

Frequency of atrial fibrillation attacks (from baseline to weeks 4, 8, and 12)
° Significant effects: The frequency of attacks decreased by more than 70%.° Effective: The frequency of attacks decreased between 30% and 70%.° Invalid: The frequency of attacks decreased by less than 30%.° Deterioration: Increased attack frequency.

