### Criteria for discontinuing or modifying allocated interventions

The criteria for discontinuation are as follows: (1) In case of serious adverse events, the clinical experimenter should be stopped according to the doctor’s judgment. (2) If the disease worsens in the course of the disease, or there are other conditions affecting the observation of the study, the clinical experimenter should be stopped and invalid cases should be treated according to the doctor's judgment. (3) Important deviations occurred in the implementation of clinical trial protocols, such as poor compliance, making it difficult to evaluate drug effects. (4) The subject is unwilling to continue the clinical trial during the clinical trial and proposes to the doctor in charge to withdraw from the clinical trial.

For these cases, the reasons for discontinuation shall be recorded in detail. If there is a review, the results of the last major efficacy test shall be taken as the final results for statistical analysis, and the CRF table and REDCap (Research Electronic Data Capture) shall be kept for future reference.

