### Sample size

The sample size of this study was calculated based on the analysis of data published in previous articles on the treatment of atrial fibrillation by Chinese medicine and the expected value of efficacy. It was assumed that the total efficacy rates in the study and control groups were 91.1% and 53.3%, respectively [8]. The set *α* = 0.025, *β* = 0.2, superiority limit value*δ*= 10%, and the sample size of each group will be calculated as 30 cases, considering a 20% loss to follow-up, that is, a total of 76 cases.

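### Exclusion criterion 7 is partly an outcome condition that cannot be judged at screening; as worded it allows randomised participants to be removed and conflicts with the rule for discontinued cases

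*Protocol article*

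**What the plan says.** Under Eligibility criteria, the protocol article admits patients who meet all inclusion criteria and "who do not have any of the listed exclusion criteria". Item 7 under Exclusion criteria reads "for various reasons, the efficacy cannot be determined or the data is incomplete".

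Four other places bear on how this item can operate:

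- **Timing of randomisation.** Study design and settings states: "After participants signed the consent form, they will be randomly assigned to the treatment or control group". Table 3 ticks both the eligibility check and randomisation in the screening column (day −3 to day 0) and nowhere else.
- **What efficacy is.** The primary outcome is the frequency of attacks from baseline to weeks 4, 8 and 12, graded by percentage reduction.
- **Discontinued cases.** Criteria for discontinuing or modifying allocated interventions covers serious adverse events, worsening, protocol deviations "such as poor compliance, making it difficult to evaluate drug effects", and withdrawal. For these cases: "If there is a review, the results of the last major efficacy test shall be taken as the final results for statistical analysis".
- **Expected loss.** The sample size of 76 is reached "considering a 20% loss to follow-up".

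**The concern.** An exclusion criterion should be decidable from what is known before allocation. No efficacy exists at that point, so whether efficacy can be determined becomes known only after treatment and follow-up. If anyone acts on that half of item 7, they act on a randomised participant, and the criterion sets no limit on the reason.

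This matters because completeness of follow-up is often related to how a participant fared. The protocol's own discontinuation reasons include worsening and adverse events. Removing such people can make the compared groups differ in ways that randomisation would have prevented.

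The item also gives two possible answers for one person. A participant who stops after the week 4 assessment has incomplete data, which item 7 names as a ground for exclusion. The discontinuation section takes that participant's last efficacy result into the analysis. The article does not say which rule prevails, so who counts could be settled after results are seen.

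**Working it through.** **Step 1. The passages side by side.**

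| Question | Where the protocol article answers it | Answer |
|---|---|---|
| When are the criteria checked? | Table 3 | Screening only |
| When is allocation made? | Study design and settings; Table 3 | After consent, screening column |
| When is efficacy first observable? | Primary outcome; Table 3 | Week 4 |
| What happens to a stopped participant with a review? | Criteria for discontinuing | Last efficacy result is analysed |
| What happens to a stopped participant without a review? | Criteria for discontinuing | Not stated |

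The efficacy half of item 7 cannot be applied at the only time the criteria are scheduled. The data half can, if it means screening or baseline records.

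**Step 2. The plan's own figure for loss.** Inputs from Sample size: 30 per group, 20% loss. Inflation: 30 / (1 − 0.20) = 37.5, rounded up to 38 per arm; 2 × 38 = 76, as stated. Twenty per cent of 76 is 15.2, so about 15 or 16 people, or about 8 per arm, are at issue. (The 30 per group does not follow from the stated rates, margin and alpha, which give 34 with unpooled variance at one-sided 0.025. That is a separate matter and does not affect this point.)

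**Step 3. How far removal could move a rate.** Assumptions, none of them in the protocol except the first two figures: true rate p = 0.533 in both arms (the planned control rate, so no true effect); fraction removed L = 0.20 in each arm; non-responders k times as likely to be removed as responders in the HTDJ arm; removal in the control arm unrelated to response.

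- Responders' removal risk: r = L / (p + (1 − p)k)
- Observed rate: p(1 − r) / (1 − L)

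For k = 2: r = 0.20 / (0.533 + 0.467 × 2) = 0.136; observed rate = 0.533 × 0.864 / 0.80 = 0.575. If everyone removed is a non-responder: 0.533 / 0.80 = 0.666.

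False-positive rates are from 200,000 simulated trials per row, 38 randomised per arm, pooled two-proportion z test at two-sided 0.05.

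| Removal in HTDJ arm | Observed HTDJ rate | Shift | False positive, two-sided | of which favouring HTDJ |
|---|---|---|---|---|
| k = 1 | 53.3% | 0 | 5.2% | 2.6% |
| k = 2 | 57.5% | +4.2 points | 6.5% | 5.4% |
| k = 5 | 62.0% | +8.7 points | 10.7% | 10.3% |
| Non-responders only | 66.6% | +13.3 points | 18.7% | 18.5% |

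The direction reverses if the control arm is the one that loses non-responders.

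**Step 4. The same mechanism in both arms.** With k = 2, k = 5 or non-responders only applied to both arms, both observed rates rise equally. The difference stays at about 0 points and the two-sided error at about 5.2% in each case, the same as k = 1. The inflation in Step 3 therefore comes entirely from the assumed asymmetry.

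**Step 5. The cost if removal is unrelated to outcome.** At the planned rates (91.1% and 53.3%), with the 10-point margin, one-sided 0.025 and unpooled variance, power = Φ[(0.378 − 0.10) / √(0.330 / n) − 1.96]. For n = 38 this is 84.7%; for n = 30 it is 75.5%. Not all of that gap is recoverable, because people without follow-up data carry little information even when kept.

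**The case against.** The strongest reply is that item 7 belongs to a screening list and Table 3 schedules that list only before allocation. Read that way, it can cover people whose attack frequency cannot be established or whose screening records are incomplete. This stands for the data half and shows that post-randomisation removal is not scheduled. It does not rescue the efficacy half, which has no meaning at screening.

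A second reply is that the discontinuation section is the specific rule. Once a last result is used, efficacy has been determined, so the two passages need not collide. This is a workable reading, but the article does not state it, and the incomplete-data wording still covers a participant with week 4 data only. The passages are in tension rather than in unavoidable contradiction.

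Third, participants, monitors and investigators are blinded. With no true effect, response-related removal would then be expected to act alike in both arms, and Step 4 shows no bias in that case. This stands as a limit on the figures. Asymmetry remains possible, for example through tolerability or imperfect masking, but the document gives no evidence of it.

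A reader might go further and infer that participants will be removed, so that the arms are compared on a selected subset; that those without a review are dropped; or that the same people leave the safety comparison. The document supports none of these. No section says that randomised participants are removed under item 7, the discontinuation section is silent on cases without a review, and adverse events are to be monitored throughout the trial.

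**Conclusion.** The concern holds as a wording defect with a real consequence if the item is applied literally. Half of item 7 is an outcome condition placed among eligibility criteria. It allows open-ended removal after randomisation, and it is not reconciled with the rule for discontinued cases. This is something the article states, not a detail left to an analysis plan.

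The size and direction of any bias cannot be derived from the document. The range of about +4 to +13 points rests on no true effect, a 53.3% rate, the whole 20% loss allowance being removed under item 7, and response-related removal in one arm only. The discontinuation rule would keep some of those people, so the upper end is an extreme. It would be wrong to read the false-positive rates of up to about 18.7% as a forecast: with the same mechanism in both arms they return to about 5.2%, and the cost is power alone.

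**What to change.** 1. Delete item 7, or limit it to information available before randomisation, for example that baseline attack frequency cannot be established at screening.
2. State that no randomised participant is removed from the primary comparison because follow-up efficacy is missing or undeterminable.
3. Reconcile the discontinuation section with that statement, including participants who have no review. The method for handling missing values can be left to the statistical analysis plan.
4. Since recruitment began in April 2020, report by arm, with reasons, anyone already removed under item 7.

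The cost is a short amendment and a small amount of extra analysis and reporting, with no extra patients or visits. The downside is that reported response rates may be slightly lower.

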### Who will take informed consent?

A study investigator or medical staff member that has received adequate training will provide the participant with extensive explanations. Upon agreeing to provide consent, the participant will be invited to sign and date the informed consent form, at which time a participant identification (PID) number will be assigned to facilitate PID throughout the study.

### Additional consent provisions for collection and use of participant data and biological specimens

Eligible participants will be invited to sign the written informed consent regarding participation in the trial (procedures, risks, options for dropping out), regarding the use of laboratory data, and regarding the collection, storage, and use of biological specimens.

### Randomization

This study uses a center-based stratification and block randomization method. The randomization sequence will be generated by study investigators who are statisticians. Patients will be allocated in a 1:1 ratio, aiming to balance baseline characteristics between the groups. Participants will be assigned a PID number, which will be used for subject identification throughout the study. Information regarding the random-number block will be delivered to the participating centers along with the intervention drugs.

### Double-blind

The study is designed as a double-blind investigation. The participants, study monitors, and study investigators will be blinded throughout the duration of the study. The PID will be the only information linked to group allocation. Random codes will be maintained by [name], associate researcher, and director of the Office of National Traditional Chinese Medicine Clinical Research Base of Longhua Hospital to ensure concealment.

### Interventions

Eligible patients will be randomized to either the treatment group or the control group. The treatment group was treated with HTDJ plus western medicine. The control group was treated with placebo granules plus western medicine. Western medicine includes cardioversion drugs and heart rate control drugs, as well as myocardial energy metabolism drugs, must be in keeping with “the 2015 Atrial Fibrillation: Current Understanding and Treatment Recommendations.” The HTDJ and placebo were produced and packed in a single batch (production batch number: HTDJ: 1070649; Placebo: 1070649) by Shanghai Wan Shicheng Pharmaceutical Co., Ltd, which has no conflicts of interest relevant to this study. The test results of drug quality were consistent with the Chinese Medicine Standards of the State Food and Drug Administration. The placebo is composed of 10% crude HTDJ and 90% starch, which have the same appearance and scent as the active treatment drugs. Participants will take one bag twice a day for 4 weeks, while avoiding oral administration of other Traditional Chinese Medicine for efficacy evaluation. Then, do not accept Traditional Chinese Medicine, only western medicine treatment, followed up for 8 weeks, another clinical evaluation.

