### Observation records of adverse events

During the trial period, the adverse event record form should be filled in truthfully. The occurrence, severity, duration, measures taken, and outcome of the adverse event should be recorded. Adverse events should be recorded in the designated clinical case observation form (CRF) adverse event form. The person uses mild, moderate, and severe to describe the intensity of the adverse event and evaluates the possible association between the adverse event and the study drug and combination drug to determine whether it is an adverse reaction. When adverse events are found, the researchers will contact the project leader immediately and start the emergency treatment plan. In case of serious adverse events, the principle of “free treatment first” shall be implemented, and the report shall be reported to the organizer and the ethics committee within 24 h, and the “Serious Adverse Events Report Form” shall be filled out and signed and marked with the date. According to the severity of adverse reactions, the follow-up visit can be in hospital, outpatient, home visit, telephone, communication, and other forms.

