HTDJ is designed from the pathogenesis of AF (qi deficiency and phlegm opacities). In this prescription, Huanglian Wendan Decoction can clear away heat and dampness and treat disturbance of the gastric qi. Pinellia ternata and Pericarpium Citri Reticulatae are used to regulate qi-flowing for removing the phlegm; Poria cocos can fortify the spleen and percolate dampness. Coptis chinensis can purge intense heat and detoxicate; Chinese date can benefit the spleen and stomach. LiuJunZi Decoction can replenish qi to invigorate the spleen and remove the phlegm. On the basis of Sijunzi Decoction, increasing the dosage of Atractylodes macrocephala can improve the effect of drying dampness and resolving phlegm. Coptis chinensis, cinnamon, and Jiaotai Pill can coordinate the heart and the kidney. On this basis, adding fossilizid and concha ostreae can quiet the spirit by heavy settling. Astragalus membranaceus can tonify middle-Jiao and Qi, while dwarf lilyturf tuber can nourish yin and promote the secretion of the saliva. Herba Epimedii can mildly reinforce the kidney yang and light yellow sophora root can clear away heat and dampness. The prescription can replenish qi to invigorate the spleen and remove the phlegm, nourish the heart and quiet the spirit, coordinate the heart and the kidney, and balance yin and yang.

Clinical and pharmacological studies have shown that Jiaotai Pill has therapeutic and anti-arrhythmic effects on AF [13, 14]. Pinellia ternata and its processed products are also anti-arrhythmic [15], and Pericarpium Citri Reticulatae has vasodilatory effects that help to induce an increase in coronary flow, which may have the effect of lowering blood pressure and slowing the heart rate [16]. The effects of Coptis chinensis include blood pressure lowering, antibiosis, anti-inflammatory, anti-tumor, regulating blood lipid, and anti-arrhythmia [17]. Icariin can effectively avoid the damage of myocardial cells and vascular endothelium caused by adverse factors. In addition to inhibiting apoptosis in cardiac myocytes, icariin can also effectively regulate blood lipid and protect the cardiovascular system [18]. In addition, Huanglian Wendan Decoction has a certain therapeutic effect on coronary heart disease with rapid AF [19]. Matrine has antiarrhythmic and electrophysiological effects [20]. Artemisia apiacea is the main drug for clinical treatment of arrhythmia [21], and arteannuin has electrophysiological characteristics of antiarrhythmia [22].

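### The control product contains 10% crude HTDJ, so the trial compares HTDJ with a low HTDJ content of unknown strength, not with an HTDJ-free placebo

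*Protocol article*

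**What the plan says.** Study design and settings gives the label: "We designed this study as a randomized, double-blind, single-simulated placebo-controlled clinical trial". The title and abstract use the same description. Study objectives sets the aim as the efficacy and the safety of HTDJ added to western medicine.

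Interventions describes the control arm: "The control group was treated with placebo granules plus western medicine". It then gives the composition of that product, "The placebo is composed of 10% crude HTDJ and 90% starch", and adds a matching claim: "which have the same appearance and scent as the active treatment drugs". The regimen is stated once, with no distinction between the arms: "Participants will take one bag twice a day for 4 weeks".

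The Introduction lists pinellia, Coptis chinensis, cinnamon and sophora flavescens among the ingredients of HTDJ. The Discussion attributes anti-arrhythmic effects to Pinellia, to Coptis and to Jiaotai Pill, which it pairs with Coptis and cinnamon. It also says: "Matrine has antiarrhythmic and electrophysiological effects".

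For harms, Observation records of adverse events says that the assessor "evaluates the possible association between the adverse event and the study drug and combination drug to determine whether it is an adverse reaction".

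**The concern.** A placebo control is meant to show what happens without the test product. Here every control participant takes some of the test product for the whole treatment period. The article discloses the composition once. It does not carry it into the design label, the objective or the stated comparison, and it does not argue that the content is too small to act.

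Two readings are at stake. For efficacy, the difference between the arms is not the effect of HTDJ against none, so a small or null difference could be taken to mean that HTDJ does little when part of its effect is present in both arms. For safety, which the objective names alongside efficacy, similar adverse-event rates could be taken to mean that HTDJ is as safe as placebo. A reaction that depends little on dose could occur in both arms and leave no difference to see.

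**Working it through.** **1. The sections side by side.** The design label and the objective require a comparison with no HTDJ. The composition in Interventions gives a comparison with some HTDJ. No other section corrects the composition or calls the 10% inactive. The Discussion supports activity of components that the Introduction lists in the recipe (Coptis, Pinellia). The matrine sentence is weaker support, because the article never says which ingredient supplies matrine.

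**2. Exposure in the control arm.** From Interventions: 2 bags a day × 28 days = 56 bags. If bags weigh the same in both arms, and if 10% crude HTDJ means a tenth of the active content (both are assumptions that the article does not confirm), then 56 × 0.10 = 5.6 active-bag equivalents.

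**3. Share of the HTDJ-versus-none effect that the contrast shows.** Let the control dose be r times the test dose, with effect E(dose) and test dose 1. The share is [E(1) − E(r)] / E(1). With r = 0.10 (assumed):

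- Linear, E(d) proportional to d: 1 − 0.10 = 0.90.
- Emax, E(d) = d/(d + ED50), ED50 at 0.5 of the test dose: (0.667 − 0.167)/0.667 = 0.75.
- Emax, ED50 at 0.1 of the test dose: (0.909 − 0.500)/0.909 = 0.45.

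The article gives no dose-response information. These curves show a range and are not estimates.

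**4. What dilution would do to the planned comparison.** Sample size gives 91.1% and 53.3% response, α = 0.025, β = 0.2, a 10-point superiority margin, 30 per group and 20% loss. The last step reproduces: 30/(1 − 0.2) = 37.5, so 38 per group and 76 in total. The 30 itself does not: with unpooled variance and one-sided 0.025 the stated inputs give 33.5, so 34. That is a separate matter, but it is why power starts below 80% in the table.

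Assume that 53.3% is the response without HTDJ (the article does not say what control produced it) and that the control keeps a fraction f of the full effect. Then:

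- Control rate p_c = 0.533 + f × 0.378; difference d = 0.911 − p_c.
- Power against the margin at 30 per arm = Φ[(d − 0.10)/SE − 1.96], with SE² = [0.911 × 0.089 + p_c(1 − p_c)]/30.
- For f = 0: SE = 0.105, and Φ(0.278/0.105 − 1.96) = 75.5%.

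The last column is a plain two-sided 5% test without the margin, which is the significance level that Statistical analysis names (pooled variance under the null).

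| f | p_c | d (points) | Power vs 10-point margin | Power, two-sided 5% |
|---|---|---|---|---|
| 0 | 53.3% | 37.8 | 75.5% | 92.5% |
| 0.05 | 55.2% | 35.9 | 69.7% | 90.1% |
| 0.1 | 57.1% | 34.0 | 63.5% | 87.2% |
| 0.2 | 60.9% | 30.2 | 50.1% | 79.8% |
| 0.3 | 64.6% | 26.5 | 36.7% | 70.4% |

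The linear case in step 3 corresponds to f = 0.1.

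**5. Direction.** If response rises with dose, then E(1) − E(r) is no larger than E(1) − E(0). The efficacy contrast is at most the HTDJ-versus-none effect, so dilution works against HTDJ and cannot create a positive result.

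**The case against.** The composition is openly disclosed and tied to matching appearance and scent, which serves the blind. That is a legitimate aim, and the full protocol that the article condenses may justify the 10%. This stands as a reason to keep the product. It does not make the control HTDJ-free or bring the label and objective into line with the composition.

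Three stronger readings are tempting, and the article does not support them.

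- *That the trial compares full dose with exactly one-tenth dose.* Bag weights and the strength of crude HTDJ relative to the finished granules are missing. Only a low content of unestablished strength is supported, and every figure above that uses one-tenth is conditional.
- *That control-arm adverse events will be dismissed as placebo background, or that causality to HTDJ will be judged in one arm only.* The article states no such rule. Causality is assessed against the study drug for every event, and the Double-blind section keeps investigators blinded throughout, so a judgement restricted to one arm is not possible. The limit concerns how the between-arm comparison is interpreted.
- *That the efficacy result is invalid or tilted toward HTDJ.* Under a rising dose response the bias is conservative.

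It is also fair to say that the Discussion shows the control is not proven inert. It does not show that the control is active at this content.

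**Conclusion.** The point holds in a limited form. The control is not HTDJ-free, so the randomised contrast is HTDJ against low-content HTDJ, each on western medicine. The randomised comparison is internally sound; the claim attached to it is too wide.

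If response rises with dose, the efficacy difference is diluted by an amount the article does not allow anyone to fix: about 10% under a one-tenth dose and linearity, 25% and 55% under the two saturating curves shown. A positive result would still indicate an HTDJ effect. The effect size and a null result cannot be read as HTDJ versus none. A lack of excess adverse events cannot be read as equivalence in safety to a placebo.

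The existence of the problem rests only on the stated composition. Its size rests on assumptions about bag weight, strength, dose response and the origin of the 53.3% control rate.

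**What to change.** Keep the manufactured product and change the text:

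- In the design, objective and conclusion text, describe the control as a low-content HTDJ control and give its composition there.
- State the primary conclusion as HTDJ versus low-content HTDJ, both on western medicine.
- Add that a null efficacy difference does not show absence of an HTDJ effect, and that similar adverse-event rates do not show that HTDJ is as safe as an inert placebo.
- Report adverse events by arm without presenting the control arm as unexposed.

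The causality assessment needs no change, since it is already made blinded in both arms.

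The cost is wording in the protocol and the report. No new product and no more participants are needed, and the blind is untouched. The price is a narrower claim than placebo-controlled. The rewording does not remove the dilution; it stops the result from being read as something the trial did not measure.
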